## Abstract

**Introduction::**

By detecting the metabolic difference of the Heart and Lung meridians, the present study aims to investigate the specificity of different meridians and verify whether functional near infrared spectroscopy is validated as an add-on technique to assist diagnosis of chronic obstructive pulmonary disease (COPD).

**Methods and analysis::**

The Lung and Heart meridians are chosen as the target for comparison; accordingly, 120 eligible participants will be included and divided into the COPD group, healthy control group, and healthy intervention group. Functional near infrared spectroscopy will be adopted to measure the metabolic characteristics of the Heart and Lung meridians. On one hand, the specificity of the meridian-visceral association will be investigated by comparing the metabolic difference in the Heart and Lung meridians between the healthy control group and COPD group. On the other hand, the specificity of site-to-site association will be determined by comparing the metabolic change between the 2 meridians that induced by moxibustion in the Heart meridian and Lung meridian, respectively, in the healthy control group. The primary outcome will be regional oxygen saturation of corresponding regions along the Heart and Lung meridians.

**Trial registration::**

ClinicalTrials.gov NCT04046666.

## Introduction

1

As a major part of complementary and alternative medicine, acupuncture is frequently used alone, or as an adjunctive therapy to treat a wide range of diseases. In the past years, increasing high-quality studies of acupuncture trials have been published in influential academic journals, which indicate the efficacy of acupuncture for treating various kinds of diseases, such as chronic functional constipation,^[1]^ migraine prophylaxis,^[2]^ chronic stable angina,^[3]^ and postprandial distress syndrome.^[4]^ Thus, acupuncture is receiving increasing attention and acceptance worldwide.^[5]^

Nevertheless, as the principle theory to guild acupuncture manipulations for thousands of years, the validation of meridian theory and the existence of meridians, remain unrecognized by many researchers due to lack of evidence.^[6,7]^ Based on traditional Chinese medicine, meridians are passageways of “qi” and “blood” and connect the body surface with internal organs, thus acting as contacts, adjustments, and response systems.

After a long period of investigations, despite that the anatomical structure of meridians remains unclear, the existence of the meridian phenomenon has been confirmed.^[8]^ And multiple biophysical techniques have been adopted to verify the biological characteristics of meridians, such as the electrical, acoustic, optical, and magnetic characteristics.^[9–12]^ Nevertheless, the majority of previous studies were designed to investigate the correlation between 1 meridian and its corresponding organ, or the difference between meridians and non-meridians, the correlation and specificity between different meridians are seldom explored. Moreover, apart from the aforementioned biological properties, metabolic characteristic is also one of the major characteristics of meridians and is relatively a new research hotspot in meridian studies, which could be measured by functional near infrared spectroscopy (fNIRS). As an established approach to monitor tissue oxygenation metabolism, fNIRS is becoming a popular tool in acupuncture studies.^[13]^

In addition, it is revealed that low oxygen saturation could be observed in peripheral vessels of chronic obstructive pulmonary disease (COPD) patients, but it remains unclear whether the distribution regions of the Lung meridians is characterized by abnormal oxygen metabolism in relative to distribution regions of the other meridians or non-meridians.

Thus, the present study will use fNIRS to detect the metabolic characteristics of meridians. We choose the Lung and Heart meridians as the target for comparison, accordingly, patients with COPD and healthy subjects will be included. Based on comparison of metabolic characteristics between these 2 meridians, the present study aims to investigate the association and specificity of different meridians. Besides, it will verify whether fNIRS is validated as an add-on technique to assist diagnosis of COPD. The findings of this study are expected to add scientific evidence for traditional meridian theory and promote the selection of acupoints in practice.

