##### Inclusion criteria of COPD patients

2.3.1.1

(1)Patients should satisfy the COPD diagnostic criteria, and the level of COPD is GOLD 2 or 3 according to results of pulmonary function testing;(2)Patients are in the stable phase of COPD;(3)35 ≤ age ≤ 75 years, gender is not limited;(4)Patients have clear consciousness and can communicate with researchers normally;(5)Patients can understand the study protocol and agree to sign written informed consents.

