### Data collection and statistical analysis

2.11

SPSS 17.0 for Windows (SPSS Inc., Chicago, IL) will be used to perform statistical analysis. For data expression, numeric data in normal distribution will be presented as mean and standard deviations, and data in skewed distribution will be presented as median and interquartile ranges. For statistical analysis methods, change in continuous variables at different time points will be analyzed by repeated measures analysis of variance. The changes within the groups will analyzed via the paired samples *t*-test, whereas differences between the groups will be compared via the independent samples *t*-test. If data is in skewed distribution, nonparametric test will be applied to perform within-group or between-group comparison. Statistical significance is defined as a *P*-value less than .05.

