Second, based on comparison upon the metabolic differences of the Heart and Lung meridians in healthy adults and COPD patients, it will verify whether fNIRS is validated as an add-on technique to assist diagnosis of specific diseases that affects oxygen metabolism in tissue, such as COPD. Previous studies revealed that low oxygen saturation could be detected in peripheral vessels in COPD patients.^[29–31]^ Similarly, based on the theory of meridian-viscera association in traditional Chinese medicine, pathological changes of internal organs will manifest in the external regions or acupoints that belongs to the diseased meridian, and this phenomenon is confirmed by a number of modern studies.^[32,33]^ Nevertheless, it remains unclear whether the distribution regions of the Lung meridians present with abnormal oxygen metabolism in relative to distribution regions of the other meridians or non-meridian paths, which will be verified by the findings of our study.

Third, various kinds of measures will be made to minimize the confounding factors that affect the tissue oxygen metabolism. In details, an experimental room with controlled temperature and humidity is set up and participants are asked to rest for a long period to adapt to the environment. All fNIRS examinations are performed at about the same period of the day. Meanwhile, stimulating food or drink, and exercise are restricted before fNIRS examinations. Fundamental physiological parameters will be measured before and immediately after fNIRS examinations, with the aim to eliminate the possibility that the change of oxygen metabolism is resulted from significant change of fundamental physiological parameters in normal state. Moreover, in order to minimize individual differences, the ratio of participant gender is controlled as 1:1 and the age between the COPD group and the healthy group will try to be matched as much as possible.

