Nevertheless, several limitations of the present study should be emphasized. First, due to the exploratory nature as a pilot trial, the study involves a small sample size. Nevertheless, this pilot study will determine whether the feasibility of the study design is validate and provide data for a large scale study in the future. Second, although various measures will be adopted to minimize external and internal factors that affect tissue oxygen metabolism, given that individual differences might be inevitable in some cases, which will reduce the reliability of fNIRS results in a certain extent.

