## Conclusions

4

By comparing the metabolic characteristics of the Heart and Lung meridians via fNIRS, the present case-controlled trial aims to investigate the association and specificity of different meridians. Besides, it will verify whether fNIRS is validated as an add-on technique to assist diagnosis of COPD. The findings of this study are expected to bring scientific evidence for traditional meridian theory and promote the selection of acupoints in clinical practice.

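### A small comparison of known COPD patients with screened healthy volunteers, analysed by group-difference tests, cannot show that fNIRS is valid as an add-on diagnostic test

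*Protocol article*

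**What the plan says.** The diagnostic aim appears four times. The Abstract gives it as one of two aims. The Introduction says "it will verify whether fNIRS is validated as an add-on technique to assist diagnosis of COPD", and the Conclusions repeat it. The Discussion widens it beyond COPD: "it will verify whether fNIRS is validated as an add-on technique to assist diagnosis of specific diseases" that affect tissue oxygen metabolism, with COPD as the example.

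The Discussion also says what the answer will rest on: "based on comparison upon the metabolic differences of the Heart and Lung meridians in healthy adults and COPD patients, it will verify whether fNIRS is" (the sentence then completes the diagnostic claim). Section 2.11 supplies the tests. Over time, "change in continuous variables at different time points will be analyzed by repeated measures analysis of variance"; for independent groups, "differences between the groups will be compared via the independent samples" t-test. Paired t-tests serve within groups, and nonparametric tests replace these when data are skewed. Section 2.7 makes regional oxygen saturation (rSO2) the primary outcome, with no cut-off or accuracy measure.

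Cases must already meet COPD diagnostic criteria and be stable, and "the level of COPD is GOLD 2 or 3 according to results of pulmonary function testing" (Section 2.3.1.1). Other major lung diseases are excluded (Section 2.3.2.1). Healthy volunteers must bring a medical report ruling out major respiratory and other disease (Section 2.3.1.2). The limitations paragraph of the Discussion says that "due to the exploratory nature as a pilot trial, the study involves a small sample size" and that its data will inform a later large study.

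**The concern.** There are three separate problems.

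1. **Wrong quantity.** A test of means asks whether two distributions differ in location. A diagnostic claim needs to know how well a value classifies an individual. A significant difference is compatible with heavily overlapping distributions.
2. **Wrong population.** Sampling known cases and screened healthy people separately leaves out everyone for whom a diagnostic aid would be used: people with suspected COPD, or with another respiratory disease that resembles it. Accuracy estimated in such extremes tends to be too high.
3. **Conflicting status.** Verifying that a technique is validated is a confirmatory claim. The same article describes an exploratory pilot.

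At stake is what the trial will be said to have shown. The Introduction and Discussion already report low peripheral oxygen saturation in COPD, so a group difference in rSO2 would be unsurprising. On the basis the Discussion sets out, such a difference could be presented as validation of a diagnostic aid.

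**Working it through.** **Inputs from the article.** Section 2.2: 120 participants, 1:1:1, so 120/3 = 40 per group; the diagnostic contrast is 40 COPD against 40 healthy controls. Section 2.11: significance at P < .05. Section 2.2 gives no effect size, SD, power or accuracy target, so the figure of 120 cannot be reproduced.

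**Assumptions (not in the article).** Two-sided test, one marker, and normal data with equal variances in the two groups. The results illustrate scale; they do not predict the trial's result.

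**Step 1: smallest significant difference.**

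d = t(0.975, 78 df) × √(2/40) = 1.991 × 0.2236 = 0.445 SD.

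**Step 2: discrimination at a given difference.** AUC = Φ(d/√2). Sensitivity at 90% specificity = Φ(d − 1.2816).

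| Situation | d | AUC | Sensitivity at 90% specificity |
|---|---|---|---|
| Just significant | 0.445 | Φ(0.315) = 0.62 | Φ(−0.836) = 20% |
| Detectable with 80% power | 0.634 | Φ(0.448) = 0.67 | Φ(−0.648) = 26% |

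The normal approximation for 80% power gives d = (1.960 + 0.842) × 0.2236 = 0.626, with the same AUC to two decimals. At a cut-off midway between the means, sensitivity and specificity both equal Φ(d/2): 59% at d = 0.445 and 62% at d = 0.626.

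**Step 3: precision with 40 per group.** The Hanley–McNeil variance is [A(1−A) + 39(Q1−A²) + 39(Q2−A²)]/1600, where Q1 = A/(2−A) and Q2 = 2A²/(1+A). For A = 0.75:

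- Q1 = 0.600, Q2 = 0.643, A² = 0.5625
- variance = (0.1875 + 1.4625 + 3.1339)/1600 = 0.00299, so SE = 0.055
- 95% CI half-width = 1.96 × 0.0547 = 0.107, giving about 0.64 to 0.86

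A larger effect, d = 1.0, gives AUC 0.76 with a 95% CI of 0.65 to 0.87. An observed sensitivity of 32/40 (80%) has an exact 95% CI of 64% to 91%.

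**Step 4: what the design can identify.** No arithmetic is needed here.

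- *Validity in use* requires participants whose COPD status is in doubt. Sections 2.3.1 and 2.3.2 admit none.
- *Add-on value* is information beyond the existing work-up. Every case enters already diagnosed and graded by lung function testing, and every control enters with respiratory disease ruled out. Eligibility has already separated the groups, so there is no residual uncertainty for fNIRS to reduce.
- *Attribution to disease* is also weak. COPD patients keep their treatments while healthy participants may take no medication (Section 2.6.4). Eligible ages are 35–75 against 20 and over, with age matching only attempted (Discussion). Outcome assessors are unblinded (Section 2.5).

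**The case against.** The strongest reply is that this is a condensed article. ROC analysis, cut-offs and the choice of marker are commonly left to an analysis plan, which may exist, so their absence from Section 2.11 proves little. That is right, and the point does not rest on it. The article itself bases the diagnostic conclusion on the group comparison, and no added analysis would supply patients with suspected disease or an increment over lung function testing.

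Second, the diagnostic aim is subordinate. The Introduction and Conclusions put it after meridian specificity, and the stated hypotheses and primary outcome do not concern diagnosis. This is a fair limit: the main comparisons, recruitment and measurements are unaffected. It remains one of the two aims in the Abstract and is repeated in the Conclusions.

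Third, the article discloses its pilot status, and case-versus-healthy sampling is a usual early step. Both are true, and both argue for exploratory wording. Asking whether fNIRS is validated presumes no positive answer, but the study cannot supply a reliable one.

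Fourth, the just-significant case is the least favourable one, no document shows that the true effect is that small, and four sites might discriminate better together. This also stands. The figures show what significance is compatible with. They put no ceiling on fNIRS, and the article nowhere states that P < .05 means validation.

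**Conclusion.** The concern holds. The planned comparison can show that mean rSO2 differs between the groups. With a suitable analysis it could also give an early, probably optimistic, estimate of discrimination. It cannot establish that fNIRS is valid for diagnosing COPD or that it adds to existing tests. With 40 per group, a significant result is compatible with an AUC as low as 0.62 and 20% sensitivity at 90% specificity, and an AUC of 0.75 would be known only to about ±0.11. Those figures assume a two-sided test, a single marker and equal-variance normal data. The design argument needs none of these assumptions. The correction is needed because a declared aim and conclusion, not a detail of method, lacks support.

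**What to change.** 1. In the Abstract, Introduction, Discussion and Conclusions, remove the aim of verifying diagnostic validation. Restate it along these lines: *to explore whether Lung-meridian rSO2 discriminates adults with stable GOLD 2–3 COPD from healthy adults*. Drop the extension to other diseases.
2. Add one analysis of data already being collected: the ROC AUC with its 95% CI for a single marker named in advance, either mean Lung-meridian rSO2 or the Lung-minus-Heart difference. Adjustment for age and sex is advisable because age matching is only attempted; if it is judged too much for a pilot, give the unadjusted AUC with the age and sex distributions beside it.
3. State in the limitations that sampling known cases and healthy volunteers overstates accuracy, and that no add-on value can be claimed.

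The cost is some rewording and one extra analysis, with no new participants or measurements. The trade-off is a more modest stated claim.

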## Methods and design

2

### Study design

2.1

This study is designed as a prospective and clinical controlled trial. Eligible participants will be divided into the COPD group, healthy control group, and healthy intervention group. The study flowchart is presented in Figure 1 and the schedule for participant screening, interventions, and outcome assessments is shown in Table 1. The report of this protocol will strictly follow the guideline of the Standards for Reporting Interventions in Clinical Trials of Acupuncture.^[14]^

**Figure 1 F1:**
[figure not shown]
Study design flowchart. COPD = chronic obstructive pulmonary disease, fNIRS = functional near infrared spectroscopy, rSO_2_ = regional oxygen saturation.

**Table 1 T1:**
[figure not shown]
Trial schedule for enrollment, intervention, and assessments.

### Sample size calculation

2.2

This study is a clinical trial that aims to measure the biological characteristics of meridians in COPD patients and healthy adults. Compared with common clinical trials that intend to evaluate the effectiveness of a specific therapy, there is no consensus on the standardization of sample size estimation for this kind of study. Thus, the sample size estimation is mainly according to similar trials^[15,16]^ and our preliminary study.^[12]^ Finally, the total number of participants is 120, and they will be divided into the COPD group, healthy control group, and healthy intervention group in a 1:1:1 ratio.

### Subjects

2.3

The subjects of this study consist of COPD patients and healthy volunteers.

#### Inclusion criteria

2.3.1

##### Inclusion criteria of COPD patients

2.3.1.1

(1)Patients should satisfy the COPD diagnostic criteria, and the level of COPD is GOLD 2 or 3 according to results of pulmonary function testing;(2)Patients are in the stable phase of COPD;(3)35 ≤ age ≤ 75 years, gender is not limited;(4)Patients have clear consciousness and can communicate with researchers normally;(5)Patients can understand the study protocol and agree to sign written informed consents.

##### Inclusion criteria for the healthy volunteers

2.3.1.2

(1)Healthy volunteers can provide a recent medical examination report, which can verify that they do not have major neurological, cardiovascular, respiratory, digestive, urinary, endocrine, and hematological diseases;(2)Age ≥20 years, gender is not limited;(3)Participants have clear consciousness and can communicate with researchers normally;(4)Participants can understand the study protocol and agree to sign written informed consents.

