##### Exclusion criteria of the healthy volunteers

2.3.2.2

(1)Participants have mental illness, history of drug abuse and alcohol dependence;(2)Participants are lactating or pregnant;(3)Participants are taking part in other studies.

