### Recruitment procedures

2.4

All participants will be enrolled from the Third Affiliated Hospital of Zhejiang Chinese Medical University. Our study will be advertised on the Internet and on posters in hospitals. Researchers will explain the aim, benefits, and potential risks of the study to participants in details. After signing written informed consents, all participants will be assessed by researchers to determine whether they can be included based on the inclusion and exclusion criteria.

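### The COPD versus healthy control comparison is open to confounding by age: control ages can fall outside the patients' range, matching is only an intention, and the stated test is unadjusted

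*Protocol article*

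**What the plan says.** Section 2.3.1.1 of the protocol article sets the age and sex rule for COPD patients: "35 ≤ age ≤ 75 years, gender is not limited". Section 2.3.1.2 sets one rule for all healthy volunteers, covering both the control and the intervention group: "Age ≥20 years, gender is not limited". The exclusion criteria for healthy volunteers (section 2.3.2.2) do not mention age or sex. Under Recruitment procedures (section 2.4), researchers assess "whether they can be included based on the inclusion and exclusion criteria".

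The Discussion (section 3) adds two measures against individual differences. On sex, "the ratio of participant gender is controlled as 1:1". On age, "the age between the COPD group and the healthy group will try to be matched as much as possible". It gives no age band, caliper, pairing or quota procedure. It does not say which of the two healthy groups is meant, or whether the sex ratio holds within each group or overall.

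The abstract describes the first main analysis as "comparing the metabolic difference in the Heart and Lung meridians between the healthy control group and COPD group". Section 2.11 names the independent-samples t-test for differences between groups, or a nonparametric test if data are skewed, at a significance level of 0.05. It mentions no covariate, stratification or matched analysis. Section 2.2 gives 120 participants in a 1:1:1 ratio.

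**The concern.** Disease status cannot be randomised. Only design (matching, restriction) or analysis (adjustment) can keep age from explaining a difference in forearm rSO2 between COPD patients and healthy controls. In this article the design part is an intention without a rule, and the eligibility range leaves room for controls who have no counterpart of similar age among the patients. The analysis part is a test that passes any remaining age difference straight into the estimated COPD effect.

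Two conclusions are at stake. One is the between-group evidence that COPD changes the metabolism of the Lung meridian. The other is the claim, in the Introduction and the Discussion, that fNIRS can assist the diagnosis of COPD. An rSO2 difference produced by age could be read as a sign of the disease in both.

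**Working it through.** **Inputs from the article.** Total 120 in a 1:1:1 ratio (section 2.2), so 120/3 = 40 per group. Significance level 0.05 (section 2.11). Sidedness is not stated; two-sided is assumed. Ages are 35 to 75 for patients and 20 or older for healthy volunteers. The article gives no effect size, SD or power, so there is no planning calculation to reproduce beyond the 40 per group.

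**Inputs that are assumptions.** The slope of rSO2 on age (0.05 to 0.2 SD per decade), the mean age gap (10 to 20 years), and the shape of the age distributions. None of these is in the article.

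**Step 1: what the age limits permit.** With ages spread evenly, purely as an illustration:

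| Group | Age range | Mean | Gap to COPD mean | Share younger than 35 |
|---|---|---|---|---|
| COPD | 35–75 | 55 | – | 0% |
| Healthy, wide | 20–75 | 47.5 | 7.5 years | 15/55 = 27% |
| Healthy, mostly young | 20–45 | 32.5 | 22.5 years | 15/25 = 60% |

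All three samples satisfy the eligibility criteria. Both healthy rows assume no matching at all.

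**Step 2: bias.** With no COPD effect, the expected difference between group means is

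bias (SD) = gap in decades × slope per decade.

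**Step 3: rejection rate of the planned t-test.** With n = 40 per group and 78 degrees of freedom, the t statistic has noncentrality bias/√(2/40). The two-sided rejection probability follows from the noncentral t distribution.

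| Gap | Slope per decade | Bias | False-positive rate |
|---|---|---|---|
| none | any | 0 | 5.0% |
| 10 years | 0.05 SD | 0.05 SD | 5.6% |
| 10 years | 0.1 SD | 0.1 SD | 7.3% |
| 10 years | 0.2 SD | 0.2 SD | 14.3% |
| 20 years | 0.05 SD | 0.1 SD | 7.3% |
| 20 years | 0.1 SD | 0.2 SD | 14.3% |
| 20 years | 0.2 SD | 0.4 SD | 42.4% |

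For the evenly spread 20 to 75 sample, the 7.5-year gap gives a bias of 0.75 × 0.05 = 0.04 SD to 0.75 × 0.2 = 0.15 SD. The rejection rate is then below 6% at the low end and 10.2% at the high end.

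**Step 4: scale.** With 40 per group, the difference detectable with 80% power is (1.960 + 0.842) × √(2/40) = 0.63 SD. A bias of 0.4 SD would be about two thirds of that.

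**Step 5: sex.** If 1:1 holds within each group, sex cannot shift the comparison and the rate stays at 5%. If it held only overall, or was not achieved, an assumed 80% versus 50% male with an assumed sex effect of 0.3 to 0.8 SD gives a bias of 0.30 × 0.3 = 0.09 SD to 0.30 × 0.8 = 0.24 SD, and a rejection rate of 6.8% to 18.5%.

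**Step 6: which comparisons are exposed.** In a Lung-minus-Heart contrast within a person, an age effect common to both meridians cancels. The moxibustion comparison, which section 2.6.2 places in the healthy intervention group, is also within person. What remains exposed is the direct COPD versus healthy control comparison and the diagnostic aim built on it.

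**The case against.** The strongest reply is that an eligibility range says who may enrol, while matching selects within that range. The healthy volunteers' list serves two groups, and the intervention group has no need of the patients' age range. A reader might infer that the age limits contradict the matching statement. They do not: a wide shared range can coexist with matching one of the two groups. This part of the objection stands. What remains is that the matching has no rule behind it.

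A reader might also see a conflict between unrestricted sex in the criteria and the 1:1 ratio in the Discussion. There is none, since both sexes may join under a quota. Only the level at which the quota applies is unclear.

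Third, the article condenses a fuller protocol, and matching bands or covariates may be set out there or in an analysis plan. That is fair, so their absence here is not the finding. The age limits and the t-test, however, are stated in this article, and the recommendation concerns those stated rules.

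Fourth, the abstract's wording could be read as a between-group comparison of the Lung–Heart difference, in which a common age effect would cancel. Section 2.11 does not specify that contrast, it would not remove an age effect that differs between the meridians, and the diagnostic aim does not rest on it alone.

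Finally, the Discussion calls the study an exploratory pilot and concedes that individual differences may reduce reliability. This lowers the urgency but does not remove the weakness.

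**Conclusion.** The point holds as an exposure to confounding by age in the COPD versus healthy control comparison, and it should be fixed. It would go too far to say that the comparison is confounded: the article states an intention to match, and matching may succeed.

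The size of any bias is unknown. Under the assumed slopes of 0.05 to 0.2 SD per decade and a mean gap of 10 to 20 years, it is 0.05 to 0.4 SD, with a false-positive rate of about 6% to 42% at 40 per group. The upper end needs both the steepest slope and a 20-year gap. A still larger figure (75.5% at 0.6 SD) would need a 30-year gap, that is, controls averaging about 25 against patients at the midpoint of 55. Even best-effort matching makes that unlikely.

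One might also infer that requiring good health draws in younger controls. The article gives no figures for this, and it also excludes patients with heart disease or serious uncontrolled illness, so the conclusion does not rely on it. Sex is a matter of clarification only.

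**What to change.** 1. In section 2.3.1.2, restrict the healthy control group to 35 to 75 years. The healthy intervention group can keep its present range.
2. Frequency-match the healthy control group to the COPD group by age band as recruitment proceeds, for example 35–49, 50–64 and 65–75, and name the healthy control group as the matched one in the Discussion.
3. State that the 1:1 sex ratio applies within each group.
4. In section 2.11, replace the unadjusted t-test for COPD versus healthy control with a linear model for group adjusted for age and sex.

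Steps 1 and 2 should come before recruitment. If the age ranges barely overlap in the data, adjustment alone would extrapolate.

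The cost is an eligibility amendment for one group, a recruitment log by age and sex, and two covariates (78 residual degrees of freedom become 76 if each enters as a single term). The downside is slightly slower recruitment of older healthy controls.
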